## 1. Specific Aims

This protocol describes a study to conduct an evaluation of a package of maternal and neonatal health programs being implemented in Kenya by Jacaranda Health. The evaluation will be a randomized controlled trial (RCT) to assess the effects of a package intervention on patient and provider outcomes. The evaluation is a collaboration between the PI team (who are leading the research design and evaluation), Jacaranda Health and Innovations for Poverty Action (Kenya).

The aims of our study are as follows:

1. To assess the intervention’s impact on patient health care utilization, knowledge, and health outcomes.
2. To assess the intervention’s impact on quality of maternal and neonatal care and health care provider knowledge.
3. To assess health facilities’ readiness to provide maternal and neonatal care.
4. To assess the implementation and sustainability of the intervention.

## 2. Background and Significance

### 2.1 Provide the scientific background and rationale for the research.

Reducing maternal and newborn mortality and morbidity remains a major public health priority in many countries in sub-Saharan Africa (SSA). In Kenya, maternal mortality and neonatal mortality remain high at 3.4 and 21 per 1,000 live births respectively. A recent study suggests that more than half of the avertable maternal and neonatal deaths in low- and middle-income countries could be amenable to better quality care, but two key challenges limit health systems’ ability to improve quality of care and patient health outcomes in Kenya.

The first challenge is that providers do not always deliver high-quality care that could avert or mitigate life-threatening pregnancy and postpartum complications due to lack of knowledge and skills. Research has shown that training in emergency obstetric care is effective in improving some maternal

and neonatal outcomes, but one-off dissemination of guidelines is often insufficient to sustain improvement in providers' knowledge or practice in low-resource settings. Mentorship programs that provide hands-on and longer-term support to health workers aim to achieve sustained improvements in quality of care through developing health workers' skills and competencies. However, evaluations of their effectiveness often focus on provider knowledge or practice alone without assessing health outcomes and very few studies are conducted in SSA using experimental designs.

The second challenge is that pregnant women and mothers are often not empowered or informed to seek care at the appropriate time, which is often referred to as the First Delay in the Three Delays Model that examines barriers to obstetric care in low- and middle-income countries (LMIC). This delay in the decision to seek care has direct consequences on the survival of mother and baby and has been associated with women's knowledge of maternal and neonatal danger signs. Such delays in care-seeking could happen along multiple points in the pregnancy and postpartum continuum. Pregnant women often do not have adequate support during pregnancy as 62% of women in Kenya do not achieve 4 or more antenatal care visits, creating missed opportunities for catching signs of complications ahead of time. In the critical 6–8-week postpartum window, 43% of women in Kenya do not get a postnatal care checkup for their health. To address such delays, mobile health interventions have become increasingly popular in LMIC to provide information, encourage care-seeking, and provide support to pregnant women and mothers, but multiple systematic reviews suggest that mHealth interventions' impact on maternal and neonatal outcomes is inconclusive due to poor methodological quality and lack of studies that evaluate patient outcomes.

Given these challenges in improving quality of care, the limitations of stand-alone interventions, and the lack of rigorous evaluations, we are embarking on an impact evaluation to assess the effects of a package intervention that addresses both provider- and patient-side barriers to achieving better maternal and neonatal health outcomes.

## **2.2 Describe the significance of the research, and how it will contribute to generalizable knowledge.** (*Generalizable: Universally or widely applicable. Knowledge: Truths, facts, information.*)

The subject of the planned impact evaluation is a package of two complementary, low-cost solutions that address drivers of poor maternal and neonatal health (MNH) outcomes in Kenya developed by our in-country partner Jacaranda Health. The first - "MENTORS" - is a facility-based program that efficiently increases and sustains provider skills in basic and emergency obstetric and newborn care. The second is "PROMPTS", a digital health platform for mothers that aims to increase care-seeking behavior at the right time and place. These interventions are designed to address the quality challenges described above: MENTORS aims to equip providers with the skills to handle general and emergency obstetric situations and support providers in consistently implementing those skills, and PROMPTS aims to inform and empower pregnant women and new mothers to seek care at the right time and place. This solution package has been designed for integration in Kenyan public hospitals and demand for expansion is increasing. However, these interventions have not yet been subject to rigorous impact evaluation.

This study aims to assess the impact of the package intervention on quality of care and MNH outcomes. The findings from this study will contribute to the evidence on 1) what facility, provider, patient factors would affect quality of care and MNH outcomes and 2) the effectiveness of m-Health and training interventions in similar settings. We plan to publish the study findings in research journals.

### 3. Research Locations and Collaborating Sites

*Research Locations refer to the geographic location that the research will take place, not to the institutions or researchers you may be collaborating with. All Research Locations should be listed in ESTR as a [Research Location](#). Collaborating Sites refer to institutions or researchers that are also taking part in the research study. All Collaborating Sites should be listed in ESTR as a [Participating Site](#).*

#### 3.1. Where will the research activities take place? (check all that apply)

|                                     |                                                                                                                                                                                   |
|-------------------------------------|-----------------------------------------------------------------------------------------------------------------------------------------------------------------------------------|
|  | At Harvard; list any non-Harvard Longwood Medical Area (LMA) Schools here: list of all Harvard Schools can be found here .                                 |
|             | At another location in Massachusetts; specify here:                                                                                                                        |
|             | In another state in the U.S.; specify here:                                                                                                                                |
|  | Internationally; specify here: Kenya                                                                                                                                       |
|             | Remotely; specify here if any remote participant will be located in the European Economic Area (EEA), European Union (EU), and/or United Kingdom (UK) while participating: |

#### 3.2. Describe the sites or locations where the research will be conducted or overseen by the Harvard PI. (If conducting the study virtually or remotely, indicate the location of the researcher who is conducting the study.)

The study sites are about 40 public or faith-based hospitals and health centers that provide maternity care services located in eight to ten counties in Kenya. The Harvard PIs will design and provide oversight for the research with close collaboration from Jacaranda Health; the field work will be carried out by the local implementation partner at Innovations for Poverty Action (Kenya).

#### 3.3. Describe plans for communication among sites regarding adverse events, interim results, protocol modifications, monitoring of data, etc. ☐ N/A.

This study is a collaboration between the Harvard T. H. Chan School of Public Health, Jacaranda Health (JH), a non-profit organization in Nairobi, Kenya, and Innovations for Poverty Action (IPA), a research nonprofit organization that serves as the study's implementing partner. Investigators and research management from Harvard and Jacaranda will hold regular management-level meetings/calls together with the IPA Research Manager and Research Associate to keep up to date on study progress and to share information across collaborating sites of unexpected negative outcomes, interim results analysis planning, protocol modifications,

monitoring of data, etc. In-person oversight from the IPA management team will be ongoing throughout the study. Additionally, there will be opportunities for enumeration staff to have in-person group feedback sessions. The Research Manager and Research Associate at IPA will stay in frequent communication with the investigators about any issues related to data quality, adverse events and protocol modifications. Any issues will be reported to the investigators within 24 hours.

**3.4. Describe any local (international or state) laws, regulations, and/or customs affecting the research (e.g., age of majority, mandatory reporting requirements, etc). ☐ N/A.**

Oversight of research in Kenya involving human subjects requires two levels of approval: (1) Approval is required at the organizational level by Institutional Ethics and Review Committees (IERCs) and (2) section 17 (1) of the Science, Technology and Innovation Act, 2013 requires all persons intending to undertake research in Kenya to apply to the National Commission for Science, Technology and Innovations (NACOSTI) for the grant of a Research License.

Those under 18 years of age (but at least 15 years of age) who are married, a mother, pregnant, or a household head are considered a mature minor in Kenya. Mature minors are considered adults in the study setting and can consent on their own.

**3.5. Identify any approvals or permissions required of collaborating institutions, community leaders, or government officials, including approval from another IRB or local research ethics committee. Upload copies to the “Study-Related Documents” page in ESTR. ☐ N/A.**

Research ethics approval for the study with annual reviews will be obtained from the Scientific Ethics Review Unit at AMREF (Kenya) in addition to Harvard School of Public Health.

County government approval: Prior to beginning work in each county, an approval letter will be signed by the respective county health directors. The letter is signed after the in-country study team presents the study protocol to members of the county health management and research team.

Facility approval: Prior to beginning the study, each facility in-charge will review and approve the study. Letter of approval will be signed by respective hospital medical superintendent.

#### Research Associate:

- Master's degree in public health, social sciences, public policy, or related fields is desirable.
- Bachelor's degree in public health, social sciences, public policy, or related fields required.
- 4-6 research experience, in the field of maternal health, strongly preferred
- Prior work experience (>4 years) conducting field research in developing contexts
- Ability to manage and clean complex datasets, preferably, using STATA
- Ability to program complex surveys in SurveyCTO
- Excellent management and organizational skills
- Demonstrated ability to manage field teams and data collection at various levels (planning, piloting, collecting, transcription, backchecking, financial budgeting and reporting, human resources and team building)
- Flexible, self-motivating, able to manage multiple tasks efficiently, and team player
- Demonstrated ability to manage high-level relationships with partner organizations, PIs and policymakers
- Excellent communication skills with fluency in English and Swahili

#### Enumerators:

- Strong writing and analytical skills and able to work with minimum supervision.
- Experience working in research and field data collection
- Understanding and experience in collecting electronic data using tablets
- *Additional requirement for those who conduct delivery observations:* must be pursuing or graduating with a (1) Medical (2) KRCN Nursing or BscN Degree within the last 2 years, and experience in maternal and newborn care (medical, nursing and midwifery schools should be accredited by the relevant national bodies in Kenya.)

The enumerators will further receive specific in-depth training by IPA staff with clinical expertise on ethics and proper conduct expected while operating in a maternity ward. This will prepare them for how to react in various scenarios to maintain the highest ethical standards.

## 5. Study Design

### 5.1. Describe the study design type.

This study is designed as a parallel arm cluster randomized control trial (RCT). Randomization of the intervention package will occur at the facility level. Overall, 40 - 50 facilities across 8 - 10 counties will be randomized into either the intervention or control group. Facilities will be chosen to ensure sufficient geographical distance from all other facilities included in the sample.

Data will be collected at multiple points during the study period (see the table below). The baseline data collection period will last for about a month in each facility. Baseline data collection will include facility assessment, register data extraction, and health worker interviews. The MENTORS program will be rolled out in intervention facilities after the baseline data collection.

The facility-based endline data collection will occur 4-5 months after the end of baseline and will last for 1-2 months in each facility. The facility-based endline data collection will include register data extraction, health worker interviews, and observations of quality of care during labor and delivery.

Process evaluation includes extraction of administrative program data collected by Jacaranda Health to monitor intervention implementation. Jacaranda Health will share this data with us throughout the study period.

We will recruit pregnant women from antenatal care clinics during the baseline data collection period. For this sample, we will conduct two follow-up surveys by phone—one towards the end of pregnancy and another at around 7- to 8-weeks postpartum. Women enrolled from the intervention facilities will be offered the PROMPTS intervention immediately after the baseline survey.

After the endline, facilities in the control group will also receive the intervention package.

In summary, we plan to collect the following data:

|                          | Facility-Based Data Collection |                   |                | Phone Surveys with Pregnant Women Cohort |                                 |
|--------------------------|---------------------------------------|-------------------|----------------|-------------------------------------------------|---------------------------------|
|                          | Baseline                       | In-between | Endline | End of pregnancy                         | 7- to 8-weeks postpartum |
| Facility assessment      | X                                     |                   |                |                                                 |                                 |
| Register data extraction | X                                     |                   | X              |                                                 |                                 |
| Health worker interview  | X                                     |                   | X              |                                                 |                                 |
| Patient interview        | X                                     |                   |                | X                                               | X                               |
| Delivery observation     |                                       |                   | X              |                                                 |                                 |
| Process evaluation*      |                                       | X                 |                |                                                 |                                 |

\*Process evaluation will be conducted in intervention facilities only.

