- I. Facilities are eligible for the study if they 1) have at least 50 normal vaginal deliveries per month on average; 2) have at most 400 normal vaginal deliveries per month on average; 3) are owned by the government or a faith-based organization; 4) have no potentially confounding ongoing research or quality-improvement programs at the time of selection (especially mentorship or mHealth programs).
- II. Providers are eligible for the provider interview if they 1) are nurses or midwives; 2) provide maternity services; 3) have no plan to move to a different facility in the next 6 months (baseline only).
- III. Pregnant women presenting for antenatal visits are eligible for the study if they 1) are at least 15 years old; 2) have access to a mobile phone; and (3) are at least 16 weeks pregnant or in Month 5, 6, 7, 8, and 9 of pregnancy.  
Those under 18 years of age who are considered a mature minor will participate. Mature

minors are those who are married, a mother, pregnant, or a household head who are under 18 years of age.

- IV. Patients admitted for labor and delivery at participating facilities are eligible for the study if they 1) are at least 15 years old; 2) are admitted for labor and delivery at the maternity ward.

Pregnant women are excluded from the study if they 1) are presenting for conditions other than labor and delivery (e.g., patients admitted for prenatal observation or complications from abortion), 2) are immediately transferred to another hospital. We apply these exclusion criteria because of the study's focus on evaluating the intervention's impact on maternal and neonatal care in selected facilities.

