**16.2. Is there a sample size/power calculation?**

☐ No ☒ Yes: *If yes, describe the calculation and the scientific rationale, and, if applicable, by site and key characteristics such as participant demographics.*

The baseline sample size is based on the power calculation for postnatal care within 6 weeks of delivery, which is our primary outcome for patient care seeking. Based on Jacaranda's internal data, we assume that 61% of women will receive any postnatal care visit within 6-8 weeks of delivery in the absence of the intervention. Based on health information system volume data, we would expect to see 120 ANC patients new to the intervention in study facilities in a given month and we expect at least 80% of them will be enrolled into the PROMPTS intervention. We plan to enroll women over at least a one-month period to reach this target. Assuming that we can track 75% of these women postpartum regarding post-delivery outcomes, we would expect to follow roughly 58 women for this outcome in each facility. Assuming an ICC of 0.01, the minimum detectable impact is an increase in postnatal care receipt of 7 percentage points or a 11% increase in postnatal care seeking.

The endline sample size is based on the power calculation for quality of care during labor, delivery and immediate postpartum, which is our primary health worker outcome. We assume that we will be able to observe at least 100 complete deliveries during six weeks of observation in each facility at the endline. Based on the PIs recent work in Uganda and Kenya, which used a very similar technique of clinical observations of deliveries in similar health facilities, we assume that average quality of care for the control group will be 0.58 (i.e., health workers will perform just over half of the important aspects of quality of care) with a standard deviation of 0.13. Assuming an intra-cluster correlation (ICC) of 0.35 (based on baseline data from our previous work), a cluster size of 100 patients, 20 clusters per arm, alpha of 0.05, and power of 0.80, the minimum detectable impact would be 6.88 percentage point increase in quality of care or an 11.9% increase in the quality-of-care index.

**17. Costs and Compensation** ☐ N/A. *Skip to next section.*

**17.1. Identify any costs that participants may incur during the study, including transportation costs, childcare, or other out-of-pocket expenses.**

There are no other anticipated costs that participants may incur during the study.

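### Control rollout waits for the facility endline but not for the phone cohort, which on the earlier permitted schedules allows contamination of the primary care-seeking outcome

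*Protocol*

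**What the plan says.** Section 5.1 fixes the order of events. On control facilities it says: "After the endline, facilities in the control group will also receive the intervention package". On timing, the "facility-based endline data collection will occur 4-5 months after the end of baseline and will last for 1-2 months in each facility".

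The word endline refers to the facility work. The table in section 5.1 lists it under facility-based collection, in a separate block from the cohort phone surveys. Section 16.2 sizes the endline on delivery observations and plans six weeks of them per facility.

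The cohort runs on a different clock. Section 5.1: "We will recruit pregnant women from antenatal care clinics during the baseline data collection period". Baseline takes about a month per facility, and section 16.2 leaves room for more: "We plan to enroll women over at least a one-month period to reach this target". Under section 5.5, women qualify if they "are at least 16 weeks pregnant or in Month 5, 6, 7, 8, and 9 of pregnancy". The outcome at stake is "postnatal care within 6 weeks of delivery, which is our primary outcome for patient care seeking" (section 16.2), and the last cohort call falls at 7 to 8 weeks postpartum (section 5.7).

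No section sets a gap between the facility endline and control rollout, makes rollout wait for the cohort calls, or says whether enrolled control women may join PROMPTS at rollout.

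**The concern.** The release of the control arm depends on one data stream, while the primary care-seeking outcome comes from another that can finish later. PROMPTS is meant to prompt timely care-seeking in pregnant women and new mothers, which is the behaviour this outcome measures. A control woman who is exposed before her six-week window closes no longer provides an untreated comparison. The contrast then shrinks toward zero, and because the endline is timed facility by facility, the dilution could differ between facilities. Analysis cannot restore the lost comparison for women already exposed. The design has no reserve to absorb this, since 7 points is already its stated minimum detectable effect.

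**Working it through.** **1. The plan's own figure.** Section 16.2 gives a control rate of 61%, 58 women followed per facility (taken as stated), an ICC of 0.01 and a detectable increase of 7 points. The 20 clusters per arm, alpha of 0.05 and 80% power are stated there for the endline calculation. I assume that they apply to the cohort too, with a two-sided test.

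- Design effect: 1 + (58 − 1) × 0.01 = 1.57
- Effective n per arm: 20 × 58 / 1.57 = 739
- Detectable difference at 80% power: 6.97 points; power for 61% against 68%: 80%

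The stated 7 points is reproduced.

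**2. One woman's timeline.** A month is 4.348 weeks, birth is assumed at 40 weeks, and times count from the end of baseline. A woman enrolled at 16 weeks on the last baseline day:

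- delivers at 40 − 16 = 24 weeks (5.5 months);
- closes her six-week window at 30 weeks (6.9 months);
- is called at 31 to 32 weeks (7.1 to 7.4 months).

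The endline ends between 4 + 1 = 5 months (21.7 weeks) and 5 + 2 = 7 months (30.4 weeks). If it ends at month 5 she is still pregnant; at month 6 she is about two weeks postpartum; at month 7 her window has just closed and her call may still be due. A woman enrolled at 16 weeks on the first baseline day delivers at 19.7 weeks and has an open window to 25.7 weeks, so she too is exposed to a month-5 rollout.

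**3. Share of control women with an open window.** Assume enrolment s weeks before the end of baseline, with s uniform over 0 to 4.35, and gestation g uniform over 16 to 40 weeks. The window closes at 46 − g − s. At rollout time e it is open if g < 46 − s − e, so the share is the average over s of max(0, 30 − s − e) / 24.

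- Month-4 start plus six weeks: e = 17.4 + 6 = 23.4. Share = (30 − 2.17 − 23.39) / 24 = 18%.
- Month-5 start plus six weeks: e = 21.7 + 6 = 27.7. Only s < 2.26 contributes: (2.26² / 2) / (4.35 × 24) = 2.4%.

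Replacing 30 by 24 gives the share still pregnant.

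**4. Effect on the contrast.** The upper bound gives every woman with an open window the full effect: 7 × (1 − share). The scaled version credits only the fraction of the six-week window that remains, which averages 7.4% over all control women for the month-4 start and 0.3% for the month-5 start. Power uses 739 per arm.

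| Endline schedule | End (weeks) | Window open | Still pregnant | Upper bound: points (power) | Scaled: points (power) |
|---|---|---|---|---|---|
| 4 months + 1 month | 21.7 | 25% | 2.5% | 5.2 (56%) | 6.1 (69%) |
| 4 months + 6 weeks | 23.4 | 18% | 0.2% | 5.7 (63%) | 6.5 (74%) |
| Ends at month 6 | 26.1 | 7% | 0% | 6.5 (74%) | 6.9 (79%) |
| 5 months + 6 weeks | 27.7 | 2.4% | 0% | 6.8 (78%) | 7.0 (80%) |
| 5 months + 2 months | 30.4 | 0% | 0% | 7.0 (80%) | 7.0 (80%) |

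**5. Sensitivity to gestation.** If women enrol at 16 to 28 weeks, the divisor is 12 and the shares double: about 37% and 5% on the two six-week schedules, and 51% for a month-5 end.

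**The case against.** A reader might infer that the primary outcome will be contaminated: that control rollout starts before cohort women deliver, that about a quarter of them are affected, and that power falls to about 56%. The documents do not support that reading, for four reasons.

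- **Schedule.** The 25% needs the shortest schedule, ending at month 5. Section 16.2 plans six weeks of observation. A facility at the eligibility floor of 50 vaginal deliveries a month would need 100 / 50 = 2 months for 100 deliveries, which moves the end to month 6 or 7, where the share is 7% or nil.
- **Still pregnant.** This applies to 0.2% on the month-4 six-week schedule, and to 2.5% even at a month-5 end.
- **Route.** Section 5.7 describes PROMPTS enrolment only for women from intervention facilities. Nothing says that control cohort women would be enrolled at rollout. MENTORS acts on provider skills, and a few weeks of it may move postnatal care-seeking little.
- **Timing and dose.** Rollout after the endline is a floor, not a date. After a month-4, six-week endline, a lag of 30 − 23.4 = 6.6 weeks would clear the last window (40-week births, enrolment within baseline). Women exposed late in their window could hardly gain the full effect.

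All of this stands, and it limits the size. It does not close the gap: the protocol states no lag and no protection for the cohort, and a month-4 start with immediate rollout complies with it. Reading endline to include the cohort calls would remove the problem, but the section 5.1 table and section 16.2 use the word otherwise.

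**Conclusion.** The concern holds as a sequencing gap. Section 5.1 permits contamination of the primary care-seeking outcome on the earlier schedules, with bias toward no effect. On the planned six-week endline, about 18% of control women have an open window for a month-4 start and about 2% to 3% for a month-5 start. Across the permitted schedules the share runs from about 25% to 0%.

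The loss for a month-4 start lies between the scaled figure (6.5 points, power about 74%) and the upper bound (5.7 points, about 63%) if control women are in fact exposed. For a month-5 start it is negligible.

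These figures rest on an assumed gestation distribution, 40-week births, a one-month baseline and immediate rollout. Earlier enrolment in pregnancy, later births or a longer enrolment period raise them; any rollout lag lowers them. The protocol does not give enough to fix the actual size.

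**What to change.** Add to section 5.1: a control facility receives the package only after both its facility endline and the last 7-8 week postpartum call to its cohort women are complete. At a minimum, state that enrolled control-cohort women are not enrolled in PROMPTS until that call; this leaves any spillover from MENTORS in place.

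The cost is one sentence and a later control rollout. With the last call at 32 weeks (7.4 months), the wait is up to 7.4 − 5 = 2.4 months after the earliest endline end and up to 7.4 − 7 = 0.4 months after the latest. On the six-week schedules it is up to 32 − 23.4 = 8.6 weeks or 32 − 27.7 = 4.3 weeks. The wait is longer if births pass 40 weeks or enrolment exceeds one month. With no overlap, the 7-point detectable effect at about 80% power stands.
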